# Effectiveness of peer support to increase uptake of retinal examination for diabetic retinopathy: study protocol for the DURE pragmatic cluster randomized clinical trial in Kirinyaga, Kenya

**DOI:** 10.1186/s12889-018-5761-6

**Published:** 2018-07-13

**Keywords:** Diabetes mellitus, Diabetic retinopathy, Diabetes support groups, Retinal screening, Blindness, Health education, Self-efficacy theory, Peer-support, Kenya, Africa

## Abstract

**Background:**

All patients with diabetes are at risk of developing diabetic retinopathy (DR), a progressive and potentially blinding condition. Early treatment of DR prevents visual impairment and blindness. The natural history of DR is that it is asymptomatic until the advanced stages, thus annual retinal examination is recommended for early detection. Previous studies show that the uptake of regular retinal examination among people living with diabetes (PLWD) is low. In the Uptake of Retinal Examination in Diabetes (DURE) study, we will investigate the effectiveness of a complex intervention delivered within diabetes support groups to increase uptake of retinal examination.

**Methods:**

The DURE study will be a two-arm pragmatic cluster randomized clinical trial in Kirinyaga County, Kenya. Diabetes support groups will be randomly assigned to either the intervention or usual care conditions in a 1:1 ratio. The participants will be 700 PLWD who are members of support groups in Kirinyaga. To reduce contamination, the unit of randomization will be the support group. Peer supporters in the intervention arm will receive training to deliver the intervention. The intervention will include monthly group education on DR and individual member reminders to take the eye examination. The effectiveness of this intervention plus usual care will be compared to usual care practices alone. Participant data will be collected at baseline. The primary outcome is the proportion of PLWD who take up the eye examination at six months. Secondary outcomes include the characteristics of participants and peer supporters associated with uptake of eye examination for DR. Intention-to-treat analysis will be used to evaluate the primary and secondary outcomes.

**Discussion:**

Eye care programs need evidence of the effectiveness of peer supporter-led health education to improve attendance to retinal screening for the early detection of DR in an African setting. Given that the intervention combines standardization and flexibility, it has the potential to be adopted in other settings and to inform policies to promote DR screening.

**Trial registration:**

Pan African Clinical Trial Registry PACTR201707002430195, registered 25 July 2017, www.pactr.org

## Background

The global prevalence of diabetes has escalated in recent decades, with important implications on the health system. In 2015 the International Diabetes Federation estimated that there were 415 million people with diabetes aged 20–79 years (global prevalence of 8.8%), and this is predicted to increase to 642 million by 2040 (global prevalence of 10.4%). [1] The incidence and prevalence of diabetes is increasing disproportionately faster in resource-poor regions and 75% of people living with diabetes currently reside in low- and middle-income countries. [1–3] This dramatic increase in incidence is occurring in both rural and urban areas. [4] The regional prevalence for Africa was 3.8% in 2015, and the number of people with diabetes in this continent is expected to increase by 140% between 2015 and 2040. [1] In Kenya, the STEPwise survey for risk factors of non-communicable diseases in 2015 found a diabetes prevalence of 2% in the population 18–69 years, and 5.4% in the population 45–59 years. [5]

All patients with diabetes are at risk of developing diabetic retinopathy (DR), the most severe and progressive ocular complication of diabetes. One third of patients with Type 2 diabetes have DR while 10% of them have sight-threatening DR, which represents a significant public health concern. [6, 7]. A population-based study in Nakuru county, Kenya found that 35.9% of people living with diabetes (PLWD) have DR [8]. Visual impairment and blindness from DR is preventable mainly through early detection and timely treatment. Since DR is asymptomatic until the advanced stages, regular retinal screening is of paramount importance. DR meets the Wilson and Jungner (1968) criteria for screening, and current clinical guidelines support annual screening [9–12]. Participation of PLWD in regular retinal screening, has been shown to be clinically effective in preventing blindness and is also cost-effective. [13, 14]

In developed countries, health systems have formal surveillance programmes for detection of DR. Kenya does not have a national population-based DR screening service where PLWD are systematically invited for screening, but opportunistic screening is available in various hospitals. Importantly, participation and re-participation rates in screening for DR are sub-optimal in Kenya and other resource poor settings. [15–22]. The determinants of the attendance to retinal examination are complex and include both supply and demand factors. [23, 24] For instance, a Tanzanian study found that PLWD also have limited awareness on diabetic retinopathy, particularly on the need for annual eye examination [25]. This is a barrier that appropriate demand side interventions could address. A health system assessment conducted before this study has shown that 87% of PLWD in Kenya have an unmet need for *annual* retinal screening. [22] One of the gaps associated with this is the lack of strong links between diabetes services and eye care services. There is need for context-specific pragmatic solutions to address this gap.

A systematic review of interventions to increase diabetic retinopathy screening attendance reported that several strategies are effective, including those targeting the patient (e.g. increasing patient awareness), the health care practitioner (e.g. improving adherence to recommendations) or the organization (e.g. improving patient records) [26]. Members of diabetes support groups (DSGs) are a population subgroup that might benefit from additional support to initiate screening, and adhere to re-screening. Targeting screening interventions towards PLWD in DSGs provides a timely opportunity for three reasons. Firstly this is a community resource that is already available in the community setting. Secondly this population is likely to consider health as an important rationale for behaviour change and the health seeking behaviour of members is potentially malleable to change through peer support. Peer support refers to the provision of emotional and informational support from a created social network member who is considered an equal and who has characteristics similar to the target population. [27] Thirdly it is an economical, culturally-sensitive and flexible intervention for improving diabetes care and outcomes. [28, 29]

Self-efficacy is a direct predictor of health behaviour, according to the social cognitive theory and the self-efficacy theory [30] [31]. Self-efficacy is a predictor of uptake of screening for DR among PLWD. [32] Interventions that improve patients’ self-efficacy decrease perceived barriers and improve the likelihood of initiating the desired health behaviour. There are four main sources of self-efficacy [31]: (i) Successful performance accomplishments (e.g. having attended a previous eye examination) (ii) vicarious experience (e.g. learning that peers have successfully attended an eye examination) (iii) verbal persuasion (e.g. encouragement and recommendation to go for an eye examination by a trusted person, such as a peer or a health care worker) and (iv) psychological cues (decreased sense of isolation of PLWD interacting with a peer, or increased awareness of the risk of DR after receiving educational messages on DR). Fig. 1 shows how self-efficacy for taking a retinal examination might improve through peer support in the Uptake of Retinal Examination in Diabetes (DURE) study.

**Fig. 1 Fig1:**
[figure not shown]
Peer support and self-efficacy for retinal examination

### Rationale

Although there is evidence that peer support improves glycaemic control and quality of life among adult PLWD, and that peer support is both cost-effective and flexible [33], evidence on whether or not it would increase uptake of eye examination in an agrarian African population is lacking. DURE study aims to provide this evidence.

The development of the intervention has been informed by the following:i.A review of the literature on peer support in diabetes [34–42] and other chronic conditions in resource poor settings. [43–51] There is evidence that peer approach is widely used in the management of diabetes, to promote  physical activity, healthy eating and improvemt in glycaemic control.ii.The results of a recent published meta-analysis of randomized clinical trials on effectiveness of peer-support for glycaemic control in Type 2 diabetes [52] which concluded that peer support had a significant impact on improving HbA_1c_ levels in patients with poor glycaemic control.iii.A health system assessment in three counties of Kenya conducted before this study showed that services for DR are underutilised: 74% of PLWD have *never* had a retinal examination in their lifetime, and 76% have *never* had a recommendation for an eye examination by their diabetes care provider [22].iv.Evidence that improving health literacy, provider patient interaction and linking patients to health care improves patients’ self-efficacy and glycaemic control. [42, 53, 54]

### Aim

To evaluate, by means of a pragmatic cluster randomized controlled trial, the effectiveness of a peer supporter- led community education programme in Kirinyaga county, Kenya.

### Research questions

To what extent can health education delivered by peer supporters increase the demand for annual retinal examination among PLWD?What are the contextual factors that determine the effectiveness of the intervention?

### Hypothesis

The hypothesis is that the proportion of PLWD having a retinal examination for DR is higher in diabetes support groups (DSGs) allocated to the peer supporter-led educational package than in DSGs randomized to the usual standard of care.

## Methods

### Design

This is a two-arm pragmatic cluster randomized controlled trial with additional process evaluation. It is a complex intervention to empower patients to undergo an annual eye examination. It is complex because those delivering and receiving the intervention require to demonstrate different behaviours and to engage in multiple interactions. [55] Its design is guided by the Medical Research Council framework for complex interventions, available at https://mrc.ukri.org/documents/pdf/complex-interventions-guidance/ [55].

The study will be conducted in accordance with the Consolidated Standards of Reporting Trials (CONSORT) 2010 statement and its extension to cluster randomized clinical trials (cRCTs). [56, 57] The cRCT design is adopted for the following reasons: (i) to reduce the effect of intervention contamination, as compared to an individually randomised trial, as patients in the same DSG often interact with one another (ii)to make it feasible to study the effect of the intervention at the individual level and the cluster level.

### Definition of eye examination for DR

We define this test as: measurement of visual acuity and a retinal examination through a dilated pupil conducted by an eye care worker (using either an ophthalmoscope, a slit lamp or a retinal camera). Retinal examination for DR and DR screening in this protocol are used interchangeably.

### Study setting

This trial will be conducted among the DSGs in Kirinyaga county, Kenya. The target population is members of the 16 support groups and volunteer peer supporters within these groups. Eye examination will be conducted at Kerugoya County Referral Hospital.

### Sample size calculation

We aim to randomize seven diabetes patient support groups (clusters) with an average membership of 50 each to each arm. The study thus has two arms of equal size (350 participants in each arm).This sample size has been calculated using standard formula for sample size for cRCTs and taking into consideration the primary outcome of interest [58, 59]. A 15% loss to follow-up contingency has been built into the sample size calculation. This sample size would have 80% power to detect a two-fold difference in the proportion of PLWD who take up eye exam, with a 5% level of significance. Member registers of the DSGs will be obtained from the team lead. These registers will be the frame for identification of participants for the study.

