### Inclusion and exclusion criteria

Participants will be included if they are PLWD aged 18+ years, will reside in Kirinyaga for the next 12 months, are members of DSGs in Kirinyaga, have a mobile phone and are willing to participate in the study. In addition to these criteria, peer supporters will be selected from those willing to participate as peer supporters, willing to commit two days for training and many hours of peer support, fluent in Kikuyu or Kiswahili, and have had a retinal examination for DR before the start of the study. PLWD who will be excluded are those already attending annual retinal screening, have a severe debilitating medical condition, are already on treatment for DR or do not meet the inclusion criteria.

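### The planned 350 per arm is the entire membership of seven groups, with no allowance for ineligible or unwilling members, so the stated size and its power need restating

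*Protocol article*

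**What the plan says.** The Sample size calculation section of the protocol article states: "We aim to randomize seven diabetes patient support groups (clusters) with an average membership of 50 each to each arm". From this it concludes: "The study thus has two arms of equal size (350 participants in each arm"). It claims 80% power at the 5% level for a two-fold difference in uptake, and adds: "A 15% loss to follow-up contingency has been built into the sample size calculation". It names the groups' member registers as the frame from which participants are identified.

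The Methods paragraph of the abstract gives the same total: "The participants will be 700 PLWD who are members of support groups in Kirinyaga". Table 2 (Process evaluation) also treats 700 as the number at recruitment, and takes 35 as 10% of the participants in the intervention clusters, which again means 350 recruited.

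The section on inclusion and exclusion criteria removes members of those same groups: "PLWD who will be excluded are those already attending annual retinal screening", together with people who are severely ill or already treated for diabetic retinopathy. Participants must also be adults, stay in the county for the next 12 months, have a mobile phone and be willing to take part. The Recruitment section plans to record reasons for non-consent, so some refusal is foreseen.

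**The concern.** The figure of 50 describes how many people belong to a group, not how many can be enrolled from it. Multiplying it by seven and calling the product participants assumes that every member is eligible and consents, which the eligibility section contradicts.

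The 15% contingency does not fill the gap. It is described, in the sample size section and again among the limitations in the Discussion, as cover for loss to follow-up. If ineligibility and refusal use it up before follow-up starts, nothing is left for its stated purpose.

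At stake is how the result will be read. A null result would be set against 80% power for a trial of 700, while the trial run in these 14 groups would be smaller by an amount the article does not estimate.

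**Working it through.** **Reproducing the stated size.** 7 groups × 50 members = 350 per arm; 14 × 50 = 700. Both match exactly, so participants equal total membership. A single ineligible or unwilling member, with no compensating excess in group size, takes the total below 700.

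**An illustration from the article.** The Background says an earlier assessment "has shown that 87% of PLWD in Kenya have an unmet need for" annual screening, which suggests that about 13% are already screened annually. If that held among group members (an assumption), 350 × 0.87 = 304.5 per arm would remain before any other exclusion or refusal. After 15% loss this is 304.5 × 0.85 = 258.8, against 350 × 0.85 = 297.5 as planned.

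**Can the 80% be reproduced?** No, because the control proportion and ICC are not given. It can be reached with suitable pairs. With control proportion p against 2p, two-sided 5% (sidedness is not stated) and m = 50 × 0.85 = 42.5 evaluable per group, the unclustered size needed per arm and the ICC that makes 80% exact are:

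| Control proportion | Unclustered n per arm | ICC giving exactly 80% |
|---|---|---|
| 10% | 199 | 0.012 |
| 13% | 145 | 0.025 |
| 15% | 121 | 0.035 |
| 20% | 82 | 0.064 |

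At 5% the unclustered requirement is 435, already above 297.5, so the design must have assumed something higher.

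**Power when fewer than 50 per group can be enrolled.** The formulas are:

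- Evaluable per group: m = 50 × share × 0.85
- Effective size per arm: n = 7m / [1 + (m − 1) × ICC]
- Power = Φ{[d√n − 1.96√(2p̄(1 − p̄))] / √(p₁(1 − p₁) + p₂(1 − p₂))}, with d = p₂ − p₁ and p̄ the mean of p₁ and p₂

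Worked case, 13% against 26%:

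- At m = 42.5, an ICC of 0.0255 gives n = 297.5 / 2.057 = 144.6 and power 80%.
- At a share of 87%, m = 36.98 and n = 258.8 / 1.916 = 135.1. Power = Φ[(0.13 × 11.62 − 1.098) / 0.5527] = Φ(0.747) = 77%.

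Over the whole range, with the ICC recalibrated for each control proportion:

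| Eligible-and-consenting share (assumed) | Enrolled per arm | Power, control 10% | Power, control 20% |
|---|---|---|---|
| 95% | 332.5 | 78.6% | 79.5% |
| 87% | 304.5 | 76.2% | 78.5% |
| 80% | 280 | 73.7% | 77.5% |
| 70% | 245 | 69.5% | 75.7% |
| 50% | 175 | 58.3% | 70.4% |

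Using the unpooled variance in the test changes these by half a point or less; the lowest entry becomes 58.7%. The loss of power is smaller than the loss of participants because the number of clusters is unchanged.

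**The case against.** The strongest reply is that the 80% has not been shown to be wrong, and this stands in full. A reader might infer that 80% power is out of reach. The document does not support that, for three reasons:

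- With control proportion and ICC unstated, the calculation may contain slack.
- The primary outcome is read from the eye clinic records of all participants, so people who lose contact may still have an outcome. With no loss at a share of 87%, the 304.5 per arm exceeds the planned 297.5 and power stays at about 80%.
- The county has 16 groups. Using all of them at a share of 87% gives 16 × 50 × 0.87 = 696 participants and about 82–84% power on the same assumptions. The pilot uses two clusters, and the article does not say whether they come from the 16. It is therefore too strong to say that the shortfall cannot be recovered.

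Two further inferences should be resisted. First, 14 × 50 × 0.87 = 609 is not a ceiling: the 87% describes people with diabetes in Kenya, and members of these groups may differ. Second, excluding annual attenders could lower control uptake, and an assumed 6.5% against 13% gives about 43% power at 37 per group with an ICC of 0.026. But the full planned 42.5 per group gives only 46% on those inputs, so that drop belongs to the assumed control rate, which has no source in the document.

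It may also be said that the plan only aims at these numbers, that equal arms is a normal planning statement when groups are allocated 1:1, and that an article leaves detailed power inputs to the full protocol. The point about equal arms is fair and is not pressed. The rest does not remove the conflict: the article itself equates membership with participants in one section and excludes members in another.

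**Conclusion.** The point holds for enrolment. The article's size equals full membership, its eligibility and consent rules reduce that, and its only contingency is for something else. From 14 groups averaging 50, the stated 700 is not a realistic enrolment figure, and the 80% is attached to it.

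For power the conclusion is conditional and mostly modest. If 80% is exact at 350 per arm, shares of 80–95% cost about 1 to 6 points, and shares of 50–70% cost about 4 to 22. This rests on an assumed control proportion of 10–20%, a two-fold effect, two-sided 5%, equal group sizes, the full 15% loss and seven groups per arm. The shares are assumptions too, since the article gives no figure for eligibility or consent among group members. This should be corrected, but it does not show that the trial is underpowered.

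**What to change.** In the Methods paragraph of the abstract and in the Sample size calculation section, replace 700 and 350 with the number of members expected to be eligible and to consent, counted from the registers that already serve as the frame. Carry the same number into Table 2.

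Restate power for that number per cluster after 15% loss. Give the ICC and the control proportion, the latter being the uptake expected among people who do not already attend annually. State separately the allowance for ineligibility and refusal and the allowance for loss to follow-up.

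The cost is some rewording and one recalculation. The stated size, and probably the power, will look slightly less favourable. No extra recruitment is needed.

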### Pilot study

A pilot study will be conducted in two clusters with 50 PLWD in each arm (intervention arm and control arm), selected through convenience sampling. The pilot will be conducted for 3 months and will involve: Testing study operational procedures; Implementation of the intervention in the intervention clusters; Testing study instruments for quantitative and qualitative data collection (questionnaires, observation sheets and topic guides); Outcomes evaluation. The primary outcome will be the proportion of participants in each arm that take up eye examination.

### Inclusion and exclusion criteria

Participants will be included if they are PLWD aged 18+ years, will reside in Kirinyaga for the next 12 months, are members of DSGs in Kirinyaga, have a mobile phone and are willing to participate in the study. In addition to these criteria, peer supporters will be selected from those willing to participate as peer supporters, willing to commit two days for training and many hours of peer support, fluent in Kikuyu or Kiswahili, and have had a retinal examination for DR before the start of the study. PLWD who will be excluded are those already attending annual retinal screening, have a severe debilitating medical condition, are already on treatment for DR or do not meet the inclusion criteria.

### Recruitment

Eligible participants will be recruited into the study by the research nurse, who will also obtain informed consent at the cluster level using the consent form approved for the study. Participants will be asked for consent to receive the intervent ion and for follow up. If the patient does not consent, reasons will be sought and recorded. After recruitment, a unique identifier number will be issued. All those recruited will be given an identification card which contains the name and a unique study number. They will be required to present this card at the eye clinic when they go for retinal examination. The flow diagram for the study is presented in Fig. 2.

**Fig. 2 Fig2:**
[figure not shown]
Flow diagram for the trial

### Randomization

Randomization will be done after recruitment. The randomization will be through computer generated random numbers prepared by a statistician (DM) using STATA version 15 (StataCorp 2017), away from the project site. The allocation sequence will be concealed from the other trial personnel. Block randomization with block sizes of two or four will be used to ensure that the two arms are balanced over time, and to maintain unpredictability of allocation. Masking will not be possible but only the research team will have formal knowledge of the allocation.

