The study has potential limitations. There are only 16 support groups in the county, which limits the possibility of increasing the number of clusters to further enhance statistical power. Delayed recruitment of the required sample size and loss to follow-up during the trial may be a challenge. In mitigation, a 15% loss to follow-up contingency has been built into the sample size calculation. Sample attrition can result from any inaccuracies in the data collection, such as incorrect address and telephone number information. Other diabetes studies have documented that patients were unable or unwilling to participate due to transportation issues and lack of time or interest [63]. However this is not anticipated because: alternative contact information of participants will be documented, only one visit to the eye clinic is required of participants, and the intervention is expected to build participants’ self-efficacy. Attrition bias may occur if whole clusters drop out, however this is not anticipated as the study period is short.

Despite these limitations, DURE study illustrates the tremendous potential of implementing pragmatic cluster RCTs in the diabetes support group setting. Implementing the trial in this at-risk population will be an invaluable learning opportunity. Many of the lessons learned from this experience could be useful to other research projects.

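### Blocks of two or four, meant to balance the arms over time, are the only restriction named for about 14 known groups; group size and distance to the one examining hospital are left to chance

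*Protocol article*

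**What the plan says.** All places are in the protocol article.

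- **Randomization:** "Randomization will be done after recruitment". A statistician away from the site prepares computer-generated numbers, and the sequence is concealed from other trial staff. On restriction: "Block randomization with block sizes of two or four will be used to ensure that the two arms are balanced over time". The second reason given for the blocks is unpredictability. No stratum, pairing or constraint on a group characteristic is named.
- **Sample size calculation:** "We aim to randomize seven diabetes patient support groups (clusters) with an average membership of 50 each to each arm". Group size appears only as this average. Member registers are to be obtained from the groups and used to identify participants.
- **Study setting:** "Eye examination will be conducted at Kerugoya County Referral Hospital". No group's distance from the hospital is given.
- **Discussion:** "There are only 16 support groups in the county". The article lists this as a limit on adding clusters to gain power.
- **Statistical analysis:** the comparison on the primary outcome adjusts for age, sex and baseline anthropometric measures. Baseline comparability will be checked, and an adjusted logistic model is foreseen if the arms turn out substantially imbalanced. The Cox model has a similar provision. Support-group characteristics enter only a separate analysis of factors associated with uptake.

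**The concern.** Blocking over time suits units that arrive one by one over a long period. Here the units come from a short list that exists before the trial starts, and allocation follows recruitment. Their features can be known when the list is drawn up. The restriction that would help most is balance on those features, and the plan names none.

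Two features are obvious candidates. All examinations take place at one hospital, so travel differs between groups. Group size decides how many participants each arm holds and hence whether the arms come near 350 each.

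With seven groups per arm, a visible chance difference on such a feature would be common. If the feature predicts uptake, the difference adds to the variance of the effect estimate and makes the result harder to defend. The number of groups cannot be raised to compensate.

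**Working it through.** **1. The plan's own figures.** 7 groups × 50 members = 350 per arm, and 350 × 2 = 700, as stated. The 80% power cannot be reproduced because the article gives neither control-arm uptake nor an intracluster correlation (ICC). The steps below do not depend on it, except the power cost in step 5.

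**2. Imbalance on one group-level covariate at exactly 7:7.** For a covariate with between-group SD of 1, the difference in arm means over all allocations has SD √(1/7 + 1/7) = √(2/7) = 0.535. Evaluating all C(14,7) = 3,432 allocations for 300 simulated pairs of independent, normally distributed, standardised covariates gives:

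- difference above 0.5 SD on a given covariate: about 37% of allocations (39% if the SD is computed with divisor 14 instead of 13);
- difference above 0.5 SD on at least one of two: about 60% (63% with divisor 14). Check: 1 − (1 − 0.37)² = 0.60.

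**3. The two candidate features.**

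- *Distance, as near or far.* Assume 7 of the 14 groups are far. The chance that the far groups split 5:2 or worse is 2 × (441 + 49 + 1)/3,432 = 982/3,432 = 28.6%.
- *Group size.* The article gives no spread, so assume a coefficient of variation (CV). The chance that the arm totals differ by 70 or more of 700 is about 7%, 20%, 35% and 44% at CVs of 0.2, 0.3, 0.4 and 0.5.

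**4. What an imbalance could do to the estimate.** The shift is the imbalance in SD times the change in uptake per SD, which the article does not give. For an imbalance of 0.5 SD and assumed gradients of 2, 5 and 10 percentage points per SD, the shift is 1.0, 2.5 and 5.0 points. With no gradient it is zero.

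**5. Side point: can the list end 8:6?** Assume sizes 2 and 4 are equally likely and the list is cut at 14. The chance that block boundaries fall at position 12 is 2/3 + (1/3)(1/2)⁶ = 0.672. An uneven split then needs the next block to be a 4 (0.5) with its first two places in the same arm (1/3):

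0.672 × 0.5 × 1/3 = 0.112.

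A simulation of 100,000 lists gave 11.3%. The figure depends on how the list is built: 0% if all blocks are 2 or the sizes sum to 14 (such as 4 + 4 + 4 + 2), and 33% if all blocks are 4.

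The cost in power is small. With 13% against 26% uptake (assumed), ICC 0.02 (assumed) and 50 × 0.85 = 42.5 members followed per group, power is 84.4% at 7:7 and 83.3% to 84.1% at 8:6. Over control uptake of 10% to 20% and ICC of 0.01 to 0.10, the loss is at most about 2.5 points.

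**6. What a constrained draw achieves.** Keep the best-balanced 10% of the 3,432 allocations on two covariates (343 remain). In the same simulations the median difference is about 0.10 SD and none exceeds 0.5 SD.

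**The case against.** The strongest reply is that concealed, computer-generated, blocked allocation of clusters is valid and that this is a matter of preference. That stands as far as validity goes. A reader might infer from the imbalance figures that the effect estimate would be biased, or that distance could not be separated from the intervention. Neither follows. Chance imbalance under valid randomization is part of the between-group variance, and a covariate can be adjusted for at a price. The loss is in precision and credibility.

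Second, the plan is not silent on imbalance, since the Statistical analysis section foresees adjustment. This must be credited, but it only partly answers the point. The adjustment is triggered by the observed data without a stated threshold, and the adjusters named for the primary comparison include no group-level variable.

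Third, the spread of sizes and distances is undocumented, and so is any link to uptake. The Discussion mentions transport as an obstacle in other diabetes studies but does not expect it here. This stands, and every figure in steps 3 and 4 of the working is therefore conditional.

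Fourth, the article is condensed, and randomization after recruitment could mean group by group, in which case blocking over time has some use. This too stands in part. However, the article states its restriction method and its purpose outright, and the groups are a finite, known list under either reading.

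Finally, a reader might take the possible 8:6 split as the main defect. The text does not support that weight. It states seven per arm as an aim, it is compatible with a list that sums to 14, and the power loss would be small.

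**Conclusion.** The point holds in moderate form, as something to consider. The one restriction named serves an aim of little value for about 14 groups from a known list, and nothing named balances the group features that could matter. Even at 7:7, a difference above 0.5 SD occurs in about 37% of draws for one covariate and about 60% for at least one of two. These two figures rest on seven groups per arm and independent, roughly normal covariates.

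Whether this matters in practice depends on how strongly size or distance predicts uptake, which the article does not say. The possible 8:6 split is a side remark.

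**What to change.** Once all groups are recruited, let the same off-site statistician allocate them in one step:

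1. List the 3,432 possible 7:7 allocations.
2. Keep those acceptably balanced on group size and distance to the hospital, for example the best 10%, with the criterion fixed beforehand.
3. Draw one of them at random.
4. Prespecify both variables in the primary model, in place of the adjustment triggered by observed imbalance.

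This also guarantees 7:7. The Trial status section places the trial at enrolment when the article was submitted; the change is possible as long as allocation has not been made.

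The programming is a few lines. The real costs are two. Allocation waits for the last group. Adjustment uses up to two of about 14 − 2 = 12 cluster-level degrees of freedom; going from 12 to 10 raises the 5% two-sided t value from 2.179 to 2.228, so intervals widen by about 2% (2.228/2.179 = 1.02) before any gain from the covariates.

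If blocks are kept, build the list so that the sizes sum to 14; that settles the 8:6 point alone.
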